### Phase 3: qualitative postintervention follow-up study

After the 12-month intervention phase, we will conduct focus groups and interviews with participants of the pilot study (family physicians, nurse practitioners, and clinic staff from each site). The objectives of this study will be to better understand participants' experiences with and perceived utility of the tool, readiness to adopt the tool at the point of care, and satisfaction with its implementation and use in practice. This information will inform sustained use of the tool.

## Methods

Focus groups and interviews will be conducted to provoke an informal discussion about participants' experiences and satisfaction with the osteoporosis tool and to find out their readiness to sustain the tool in their practice. Questions will include participants' perceptions on barriers and facilitators to using the osteoporosis tool at the point of care, how the tool functioned in practice, whether they plan to continue using the tool in their practice, their perceptions of the tool's impact on their practice workflow, and any suggestions for improving the tool. To minimize the occurrence of "history" (a threat to internal validity where some other influential event may happen during the intervention), we will design an accompanying questionnaire to capture all clinical practice-related activities done by physicians (*e.g.*, continuing medical education [CME] activities) during the study that might account for changes between baseline and postintervention observations. We will also incorporate participant- and site-specific demographic questions and relevant items from the four-point BARRIERS scale, which can be used to assess barriers to research utilization [30].

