#### Unit of analysis and data collection

Our unit of analysis will be based on the multiple baseline assessment of individual family practice sites rather than a single group of participants being tested repeatedly before and after the introduction of the intervention. The data set at each time point will consist of patient charts, which will represent the "episode of care" used to extract outcome data for the study. To ensure the completeness and validity of the data set at each time point, we will apply the quality-control criteria of ITS designs by Ramsay *et al.*, which recommend that 80%-100% of the total number of episodes of care (*i.e.*, patient charts) be used in the data collection [27].

Once the intervention is implemented, data will be collected on all outcomes from electronic patient records (*i.e.*, PracticeSolutions^®^) and the touch-screen tablet PCs. The purpose of the pre-intervention chart review will be to establish a stable baseline of standard practice for each site. Visit-specific data (*e.g.*, initiation of osteoporosis disease management, reason for visit) will be collected bimonthly at each site by two researchers (MK and CM). To minimize the introduction of contamination that could bias results during this phase, all data collection techniques, procedures, and data collection forms will be standardized. For calibration of reliability, these two researchers will extract data from 10 randomly selected patient charts in duplicate until their agreement reaches ≥80%, at which point they will abstract data independently. The two researchers will collect data from the touch-screen tablet PCs, which will automatically generate two electronic logs each time a patient completes the RAQ. The first log will outline dated/timed RAQ responses, and the other will summarize the content of the BestPROMPT sheet. These electronic logs will be matched against patient-visit chart data to verify the use of the tool during the visit and to map any actions taken by the physician in response to the use of the RAQ.

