#### Analysis

Results of this ITS study will focus on the impact of the intervention on the time series, which will be tested by comparing pre- and postintervention segments of the time series to estimate the magnitude and form of the impact. "Impact" on practice will be defined according to the level of change that is observed between the baseline and postintervention periods of the study. The impact of the tool for changing practice and satisfaction with the tool will also be analyzed across the three sites. Aggregated data from each two-week segment period on primary outcomes will be analyzed using the autoregressive integrated moving average (ARIMA) approach and time-series regression models [28,29]. We hypothesize that the 26 time-point baseline assessment of practice will show no pre-intervention trend. The ARIMA approach will estimate the extent to which a significant level of change occurs between the pre-intervention and postintervention phases of the study. The multiple measurement points are necessary for the ARIMA analysis to distinguish between treatment effects and secular trends. The advantage of using the ARIMA approach for analysis is that it accounts for the three major sources of noise that may confound the analysis: trend, seasonality, and random error [28,29]. Secondary outcomes and logs of patient-initiated data from tablet PCs will be analyzed using frequency analysis of site-specific data, descriptive and inferential statistics to calculate proportions and time to completion of the RAQ (*e.g.*, means with standard deviations), and independent-sample *t*-tests or analysis of variance (ANOVA) for group comparisons (*e.g.*, differences between sites for outcomes).

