### Analysis

Interviews and accompanying questionnaires will be quantitatively and qualitatively analyzed. Interview sessions will be audiotaped and transcribed verbatim. Data collection and qualitative content analyses will be guided by the constant comparative method of grounded theory methodology [31]. Two investigators will independently develop a coding scheme by identifying, classifying, and labelling the primary patterns in the content. Inter-coder reliability will be assessed using Kappa statistics, and any disagreements will be resolved by consensus. Data will be coded from transcripts using a process of open, axial, and selective coding [31,32] using NVivo 8 software (QSR International, Cambridge, MA, USA). During open coding, the constant comparative approach will be used to group the codes into categories and identify themes. Quantitative analysis of accompanying questionnaire data will be analyzed using analysis of variance for continuous variables (*e.g.*, Likert-type questions), chi-square tests for dichotomous variables (*e.g.*, yes/no-type questions), and content analysis for open-ended questions.

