### Potential limitations

Our study has several potential limitations. The ITS methodology, which was chosen for the pilot evaluation of the osteoporosis disease-management tool, is susceptible to several potential threats to internal validity. In general, we designed our methodology according to the ITS quality criteria recommended by Ramsay *et al. *to help overcome these threats and to rule out any alternative explanations of our findings [27]. Instrumentation (a threat to internal validity that could occur if the measurement method changes during the intervention and evaluation period) is a common threat in medical record data research, particularly in a multisite study. To overcome this problem, we will ensure that our databases, recording systems, observers, and outcome-measure instruments remain consistent, and they will be monitored closely for any changes that might occur over the course of the study. History is another potential threat because a change in clinical practice independent of the introduction of the intervention may occur from the influence or participation of other events and activities during the study period. For healthcare professionals and physicians in particular, these include continuing professional development activities (*e.g.*, participation in CME activities such as didactic lectures, small-group workshops, and attendance at conferences). To address this potential threat, we will collect information on continuing professional development activities using the demographic/evaluation questionnaire, which will incorporate questions targeted specifically for capturing clinical practice-related activities and events that might account for changes between baseline and postintervention observations.

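### The named remedy for concurrent events is a questionnaire given after the intervention year; it can document such events but has no stated route into the effect estimate, and an event at a site's go-live cannot be separated from the tool

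*Protocol article*

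**What the plan says.** Phase 3, Methods defines history as some other influential event during the intervention, and names a counter to it: "we will design an accompanying questionnaire to capture all clinical practice-related activities done by physicians". Potential limitations repeats the same remedy, with continuing medical education as the example: "we will collect information on continuing professional development activities using the demographic/evaluation questionnaire". No other remedy for such events is named.

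The timing follows from the Phase 3 introduction: "After the 12-month intervention phase, we will conduct focus groups and interviews with participants of the pilot study".

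The questionnaire has its own analysis under Phase 3, Analysis: "Quantitative analysis of accompanying questionnaire data will be analyzed using analysis of variance for continuous variables", with chi-square tests and content analysis for the other items. The effect of the tool is estimated separately. Under Phase 2, Analysis, the ARIMA approach is preferred because "it accounts for the three major sources of noise that may confound the analysis: trend, seasonality, and random error".

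On design, Unit of analysis and data collection says "Our unit of analysis will be based on the multiple baseline assessment of individual family practice sites". Sampling and population gives each site 26 two-week segments before and 26 after the tool. Phase 1 counts the tool as implemented once a week passes without new problems. Potential limitations says that published quality criteria were followed "to help overcome these threats and to rule out any alternative explanations of our findings".

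**The concern.** Phase 3, Methods presents the questionnaire as a way to reduce the occurrence of history. A form filled in after the intervention year cannot do that; it can only record what physicians remember. To correct the estimate, the events would need dates and a term in the time-series model, and the article describes neither. Trend, seasonality and random error, the three noise sources that the model is said to handle, do not include a one-off outside event. Study design does list history among the things the design can address, but describes it there as trend or seasonal pattern, which is a different threat from the one in Phase 3, Methods and Potential limitations.

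The primary result is a pre/post level change in practices that all receive the tool, with no comparison series named. All three belong to one Family Health Team, so a regional course or a guideline release could plausibly reach all of them. If such an event fell near go-live, its effect would be reported as the tool's effect and carried into the decision about wider testing.

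**Working it through.** **Inputs from the article.** Three sites; 26 + 26 = 52 segments per site; 26 × 2 weeks = 52 weeks, which agrees with the stated 12 months per period. Autocorrelation and effect size are stated as unknown, so the values of rho (0, 0.2, 0.4) and the event sizes below are assumptions. Effects and standard errors are in units of the SD of a two-week data point.

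**Step 1: one site, event at go-live.** Number the segments t = 0 to 51. The tool term is D = 1 for t ≥ 26, and a lasting event k segments after go-live is E = 1 for t ≥ 26 + k. At k = 0, E = D: the two columns are the same, and no date or recall can separate them.

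**Step 2: one site, event away from go-live and not modelled.** With a level term only, the share of the event that enters the tool estimate is (26 − k)/26. With a trend term it is the least-squares projection of E on D given the trend.

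| Event after go-live | Level only | Trend + level |
|---|---|---|
| k = 0 | 100% | 100% |
| k = 3 (6 weeks) | 23/26 = 88% | 58% |
| k = 6 (12 weeks) | 20/26 = 77% | 24% |

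For k ≠ 0 the event is estimable as a separate step, provided its date is known.

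**Step 3: what this does to the test.** AR(1) series, trend + level model, rho treated as known, two-sided 5%, true tool effect 0, event at go-live, 4,000 series per setting. Proportion declared significant:

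| Event size (assumed) | rho 0 | rho 0.2 | rho 0.4 |
|---|---|---|---|
| none | 5% | 5% | 6% |
| 0.5 SD | 14% | 13% | 9% |
| 1 SD | 44% | 32% | 29% |
| 1.5 SD | 77% | 63% | 53% |

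**Step 4: three sites, event common to all.** Generalised least squares with site intercepts, a common trend, the tool step at each site's go-live and a common event step. With simultaneous starts and the event at go-live, the design has rank 5 for 6 columns, so the tool effect is not estimable apart from the event. With starts 4 segments (8 weeks) apart and 26+26 points kept at each site, it is estimable:

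| Setting | SE, rho 0 | SE, rho 0.4 |
|---|---|---|
| Simultaneous starts, no event in model | 0.320 | 0.420 |
| Staggered, known event at first go-live | 0.366 (+14%) | 0.471 (+12%) |
| Staggered, known event at middle go-live | 0.411 (+28%) | 0.506 (+20%) |
| Staggered, free effect for every calendar segment | 0.464 (+45%) | 0.582 (+39%) |

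Percentages are against the first row, for example 0.366/0.320 = 1.14.

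**Step 5: different dates alone are not enough.** With staggered starts but only site intercepts and the tool step in the model, an event at the first go-live still passes 96%, 88% and 77% of its size to the tool for offsets of 0/1/2, 0/3/6 and 0/6/12 segments. With calendar-segment effects in the model this bias is 0.

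**The case against.** A reader might infer that all sites go live on the same day and that the design therefore cannot identify the tool effect. The article does not support that. It gives the number of points per site, not calendar dates. Phase 1 tailors the work to each site and ends with a criterion about reported problems, so dates may well differ. A reader might also infer that questionnaire data are barred from the model, or that the recall window is two years. Neither is stated: the text says only that activities during the study are captured and that they might account for changes. Go-live dates and model covariates are also matters that a condensed article may leave to a fuller document.

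The article further lists history as a limitation, calls the study a pilot and points to a later randomised trial. Its phrase about alternative explanations is an aim, not a result.

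Staggering is also not a full answer. It does nothing against an event specific to one site at that site's own start, and course attendance, the article's own example, is often particular to one physician. Staggering and an added control series are design trade-offs, not corrections of an error.

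All of this stands and limits the point. It does not rescue the stated remedy. The article does fix the instrument, its timing after the intervention, its separate analysis and the claim made for it. Acknowledging a threat is not adjusting for it.

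**Conclusion.** The point holds in this form. The only named counter to concurrent events is a questionnaire given after the intervention year. It can document events by recall, it cannot reduce them, and no stated analysis carries it into the time-series estimate. A lasting event at a site's go-live is fully aliased with the tool in that site's series. The multiple baseline protects against common events only if starts differ and the analysis uses the offsets; the article states neither, and simultaneous starts are not established.

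The 100% figure is exact for a permanent step in the go-live segment and falls with distance from it. The false-positive rates rest on assumed event sizes and autocorrelations and show what could happen, not what is expected. The standard errors in Step 4 assume 26+26 points per site and, except in the last row, a known event date. For a pilot this is a worthwhile and inexpensive correction, not a reason to abandon the design.

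**What to change.** 1. Have the researchers record dated education, guideline and staffing events at each scheduled data-collection visit, and reconstruct the baseline year as far as records allow.
2. Report each site's actual go-live date, and analyse on calendar time with a site-specific step date.
3. Enter dated events that lie away from go-live as model terms, or use them in a sensitivity analysis.
4. Describe the questionnaire as an aid to interpretation. Replace the claim about ruling out alternative explanations with a statement that an event at go-live cannot be separated from the tool.
5. Optionally, plan staggered starts. Four segments apart delays the last site by 2 × 8 = 16 weeks and raises the standard error by about 12-14% for a known common event at the first go-live, about 20-28% at the middle go-live, and about 39-45% with free calendar effects.

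Items 1 to 4 cost a short log, slightly more analysis work and a more modest claim.

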### Analysis

Interviews and accompanying questionnaires will be quantitatively and qualitatively analyzed. Interview sessions will be audiotaped and transcribed verbatim. Data collection and qualitative content analyses will be guided by the constant comparative method of grounded theory methodology [31]. Two investigators will independently develop a coding scheme by identifying, classifying, and labelling the primary patterns in the content. Inter-coder reliability will be assessed using Kappa statistics, and any disagreements will be resolved by consensus. Data will be coded from transcripts using a process of open, axial, and selective coding [31,32] using NVivo 8 software (QSR International, Cambridge, MA, USA). During open coding, the constant comparative approach will be used to group the codes into categories and identify themes. Quantitative analysis of accompanying questionnaire data will be analyzed using analysis of variance for continuous variables (*e.g.*, Likert-type questions), chi-square tests for dichotomous variables (*e.g.*, yes/no-type questions), and content analysis for open-ended questions.

## Discussion

The osteoporosis tool has the potential to impact clinical care and to make several contributions to the development of complex, chronic disease interventions. The clinical goal of the osteoporosis tool was to bridge the gap between current and best practice in osteoporosis disease management. The three-phased evaluation study will address this goal and illustrate how its rigorous development can lead to meeting the many challenges to developing complex interventions. Without careful consideration of system design, function, and end-user perspectives, these interventions can fail [33]. If information technology systems such as the osteoporosis tool are integrated without evaluating how they might impact end users or their existing workflow, they have the potential to be ineffective, function poorly, and result in medical or technology-induced errors [34-36]. To meet the specific needs of physicians, customization of information technology systems such as the osteoporosis tool need to match and support the workflow.

We anticipate that the osteoporosis tool will benefit both physicians and patients. This benefit may include an increased awareness for patients about osteoporosis and its associated risks, the availability of relevant information about what they can do about these risks, and the opportunity to discuss this information and a management plan with their family physician at the point of care. We believe that this component is an important step toward improved self-management.

Self-management strategies can help patients manage their medical conditions and provide patients with information, skills, and the confidence (self-efficacy) to deal with their illness [37]. Moreover, patient self-management may facilitate the sustainability of an intervention by alleviating resource burdens that might be needed to maintain the ongoing use of the tool; for example, a study found that a falls-and-fractures prevention strategy in a family practice unit delivered by clinic nurses was effective, but it could not be sustained beyond the study period [38]. We have planned for the equipment (touch-screen tablets, printers, etc.) to remain at the evaluation sites permanently so that patients and physicians can continue to benefit from the tool beyond the study period if they choose to.

Self-management is becoming increasingly important for the development of chronic disease-management interventions because seniors are becoming the fastest-growing population group [39]. This is expected to increase the prevalence of chronic diseases [40] and increase the awareness and the need for patient self-care to support chronic disease management [40,41]. As a result, there is a shift toward a new patient-physician relationship for chronic disease management, where patients are becoming their own caregivers and healthcare professionals act as consultants to support their patients in this role [42,43].

### Potential limitations

Our study has several potential limitations. The ITS methodology, which was chosen for the pilot evaluation of the osteoporosis disease-management tool, is susceptible to several potential threats to internal validity. In general, we designed our methodology according to the ITS quality criteria recommended by Ramsay *et al. *to help overcome these threats and to rule out any alternative explanations of our findings [27]. Instrumentation (a threat to internal validity that could occur if the measurement method changes during the intervention and evaluation period) is a common threat in medical record data research, particularly in a multisite study. To overcome this problem, we will ensure that our databases, recording systems, observers, and outcome-measure instruments remain consistent, and they will be monitored closely for any changes that might occur over the course of the study. History is another potential threat because a change in clinical practice independent of the introduction of the intervention may occur from the influence or participation of other events and activities during the study period. For healthcare professionals and physicians in particular, these include continuing professional development activities (*e.g.*, participation in CME activities such as didactic lectures, small-group workshops, and attendance at conferences). To address this potential threat, we will collect information on continuing professional development activities using the demographic/evaluation questionnaire, which will incorporate questions targeted specifically for capturing clinical practice-related activities and events that might account for changes between baseline and postintervention observations.

### Control of the implementation of the intervention

We anticipate that once the intervention is implemented, there will be an increase trend toward optimal practice according to guidelines. This sudden rise will likely occur from the implementation process rather than the intervention itself. We therefore chose a greater number of data points (which is also equal to the data points in the baseline assessment phase) to help neutralize the initial impact of the implementation and allow the true impact of the intervention to emerge.

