First, we will perform a workflow analysis, which will include observation of clinic staff during "typical" clinic days. Two researchers will document the patient registration process (particularly how patients are moved from the waiting area to the examination room) and estimate the average time that patients wait for their physician, the length of patient visits, and time between visits. Second, researchers and an information technologist will conduct an environmental scan to ensure appropriate equipment installation. Third, a procedures manual will be developed and customized for each site. Lastly, clinic staff (including physicians, nurses, and receptionists) will be trained on how to use and troubleshoot the osteoporosis tool. Once programming is completed and equipment installed, clinics will be instructed to begin using the tool, and observed to correct unanticipated installation, programming, or workflow interruption problems. We will consider the tool as implemented when no new problems are reported for at least one week.

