#### Sampling and population

In ITS studies, sample size calculations are related to the estimation of the number of observations or time points at which data will be collected. According to Ramsey *et al.*'s quality criteria for ITS designs, at least 10 pre- and 10 post-data points would be needed to reach at least 80% power to detect a change (if the autocorrelation is >0.4) [27]. Since the current study is a pilot, it is not known what the autocorrelation might be or what effect size the intervention is likely to produce. We therefore decided to use a relatively large number of data points to ensure that any trend or seasonal differences can be detected: 52 data points per site (where one data point = two-week segment)--26 data points before the introduction of the intervention (equivalent to 12 months' worth of two-week segments) and 26 data points after the introduction of the intervention (two-week segments for 12 months). Participants will be family physicians practicing in a solo or group practice within the Hamilton FHT and their patients at risk for osteoporosis selected according to gender- and age-eligibility criteria (*i.e.*, women ≥50 years of age, men ≥65 years of age).

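### The plan predicts an early rise caused by implementation rather than the tool, keeps it in the post series, and relies on more data points that only partly dilute it

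*Protocol article*

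**What the plan says.** The section on control of the implementation of the intervention makes a prediction: "We anticipate that once the intervention is implemented, there will be an increase trend toward optimal practice according to guidelines". It then assigns a cause: "This sudden rise will likely occur from the implementation process rather than the intervention itself". The answer it offers is a greater number of data points, equal to the number at baseline, "to help neutralize the initial impact of the implementation and allow the true impact of the intervention to emerge".

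Under Sampling and population, each site contributes 52 points, of which 26 are baseline. The rest are described as "26 data points after the introduction of the intervention (two-week segments for 12 months". No early segment is set aside. The reason given there for the series length is a different one: "We therefore decided to use a relatively large number of data points to ensure that any trend or seasonal differences can be detected".

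The Phase 2 Analysis section defines impact by the level of change between the baseline and postintervention periods, and says: "The ARIMA approach will estimate the extent to which a significant level of change occurs between the pre-intervention and postintervention phases of the study". It also names time-series regression models.

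Phase 1 includes a period of live use in which "clinics will be instructed to begin using the tool, and observed to correct unanticipated installation, programming, or workflow interruption problems". It ends after at least one week without new problems.

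**The concern.** The protocol separates two things: the effect of the tool, which it wants to estimate, and a rise caused by putting the tool in, which it does not. The second falls in the first segments after the break. A rise there raises the post-period mean and, in a model with slopes, also raises the fitted jump at the break.

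ARIMA does not remove it unaided. The Analysis section credits ARIMA with handling trend, seasonality and random error, and a one-off rise that coincides with the start of the intervention is none of these. Without a term of its own it loads on the intervention term.

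At stake is the primary result. The bias favours the tool, in a pilot meant to show whether wider testing is justified.

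**Working it through.** **Inputs from the article.** 26 baseline and 26 post points per site, each of two weeks: 26 + 26 = 52 points, and 26 × 2 = 52 weeks per phase, which agrees with the stated 12 months.

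**Assumptions.** The article gives no size or duration for the rise and says that the autocorrelation is unknown. I take a rise of height S over the first k post segments, a true tool effect of zero, and AR(1) of 0 or 0.4. The expected estimate is b = (X'V⁻¹X)⁻¹X'V⁻¹y, with y equal to S in those k segments and 0 elsewhere.

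**By hand, k = 4, AR(1) = 0.** Number the post segments 0 to 25. Their mean is 12.5, and the sum of squares about it is 26 × (26² − 1)/12 = 1462.5. The cross-product of time with the rise is (0 + 1 + 2 + 3) − 4 × 12.5 = −44.

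- Step only: 4/26 = 0.154 S.
- Common trend plus step: slope = −44/(2 × 1462.5) = −0.0150; step = 0.154 + 26 × 0.0150 = 0.545 S.
- Segmented (trend, step, slope change): slope change = −44/1462.5 = −0.030 S per segment; level change at go-live = 0.154 + 12.5 × 0.0301 = 0.530 S. Read at the middle of the post period, the same model gives 0.154 S.

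**Share of S that appears as tool effect (26 + 26 points; AR(1) = 0 / 0.4):**

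| Model and estimate | k = 4 | k = 6 | rise lasts all 26 |
|---|---|---|---|
| Step only | 0.15 / 0.22 | 0.23 / 0.28 | 1.00 |
| Trend + step | 0.55 / 0.65 | 0.76 / 0.82 | 1.00 |
| Segmented, at go-live | 0.53 / 0.64 | 0.74 / 0.80 | 1.00 |
| Segmented, mid-post | 0.15 / 0.28 | 0.23 / 0.30 | 1.00 |

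**Does a longer series neutralize the rise?** With 26 baseline points, k = 4 and AR(1) = 0, lengthening the post series from 10 to 26 points changes the share as follows:

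- Step only: from 4/10 = 0.40 to 0.15.
- Segmented, at go-live: from 1.05 to 0.53.
- Trend + step: 0.54 to 0.55, in effect unchanged.
- A rise that lasts: 1.00 at either length.

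**Effect on the test.** For k = 4 and a nominal two-sided 5% test, the false-positive rate in the step-only model is 8 to 9% if S is one standard deviation of a segment value, and 19 to 20% if S is two. Across all three level terms the ranges are 8 to 17% and 19 to 50%. The standard deviation and autocorrelation are treated as known.

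**Leaving out the first 4 post segments.** The bias falls to zero if the rise has ended by then. The standard error of the step-only estimate is multiplied by √[(1/26 + 1/22)/(1/26 + 1/26)] = 1.044 at AR(1) = 0 and by 1.071 at 0.4. For the level term at go-live the factors are 1.165 and 1.265 (trend + step) and 1.203 and 1.301 (segmented).

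**The case against.** Much of the case on the other side stands.

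- **All of the artefact reported as tool effect.** A reader might infer this, but it is true only of a rise that lasts. In the step-only model, about 80% of the height of a 4-segment rise stays out of the estimate.
- **A test of the jump at go-live.** The Analysis section speaks of change between phases and expects no baseline trend. That is closest to a step between two levels, so 0.15 to 0.22 S is the fairest figure. The 0.53 to 0.65 S and the spurious decline in slope arise only if a trend or segmented model is fitted and read at the break. The article does not fix that choice.
- **The protocol claims only that more points help.** They do, in the step-only and segmented models.
- **Contamination by Phase 1 in the tool's favour.** The documents do not support this. Phase 1 is a separate, earlier phase with its own end rule; the baseline lies before the introduction of the tool; and the section on unit of analysis and data collection ties outcome collection to the tool having been implemented. This can be read as keeping the live-use weeks out of both series, though it is not said outright. Any training or observation that did leak into the baseline would tend to raise it and so work against the tool.
- **The Analysis section will estimate the form of the impact, and the detail may sit in a plan not shown.** A transient form is allowed, but nothing commits to separating it. The point does not rest on missing detail: the article states its remedy, and that remedy falls short.

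**Conclusion.** The concern holds in limited form. The protocol names a cause other than the tool for an early rise, keeps that period in the post series, and counts the whole change between phases as impact. More points dilute a short rise but do not remove it, so the primary estimate is biased towards the tool.

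On the closest reading, a rise lasting 8 weeks (4 × 2) contributes 0.15 to 0.22 of its height. In a trend or segmented model, about 0.53 to 0.65 enters the level term at go-live. If the rise lasts, it enters in full and this single-intervention series cannot tell it from the tool.

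Height, duration and autocorrelation are assumptions, so no absolute bias can be given. For a three-site pilot that openly acknowledges the threat and partly mitigates it, this should be fixed; it does not undermine the design.

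**What to change.** 1. Pre-specify a transition window of the first k two-week post segments at each site, with k set before the data are seen (for example k = 4). Exclude it from the primary model or give it its own transient term, and estimate impact on the later segments.
2. Report the full 26 + 26 series as a sensitivity analysis.
3. State that the Phase 1 live-use weeks belong to neither the baseline nor the post series.
4. Reword the section on control of the implementation: more points dilute a short-lived implementation effect but do not remove it, and a lasting one cannot be separated from the tool.

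**Cost.** This is mainly wording. At k = 4 the standard error rises by about 4 to 7% for a step-only model and by about 16 to 30% for the level term at go-live in a trend or segmented model. Collecting for 8 more weeks would restore 26 usable post points. It would also restore a full year after the window, which matters if outcomes are seasonal. No window removes a rise that outlasts it.
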